This trial’s objective is to identify a rehabilitation program focused on education and exercise for AT that expands access to care and to identify factors that predict responses to rehabilitation. Our aims are twofold: (1) to determine the efficacy of a single-visit, PT-initiated rehabilitation program compared to a multivisit, PT-guided telehealth rehabilitation program for AT and (2) to identify early prognostic factors for individuals who experience the greatest improvement in pain and disability by 4 weeks. We hypothesize that a single-visit, PT-initiated rehabilitation program with a self-guided intervention will be as effective in improving pain and disability as a multivisit, PT-guided telehealth intervention. We also hypothesize that individuals with greater immediate (within 2 weeks) improvements in self-efficacy, pain, and disability will obtain the greatest benefits from rehabilitation.

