### Outcome Measures

To maintain blinding of outcome assessment, baseline measures will be gathered in person prior to randomization. A research assistant blinded to the treatment groups will capture outcomes after randomization. Participants will complete 3 survey-only evaluation sessions at 2, 12, and 26 weeks. Participants will complete 3 video evaluation sessions, including surveys, at 4 weeks (primary end point), 8 weeks, and 52 weeks. The video evaluation sessions will be used to capture pain with tendon-loading activities (heel raises and hops) in real time, assess heel raise performance (number of heel raises), and screen for adverse events. A visualization of measure administration can be seen in Table 2.

**Table 2. T2:** Data collection schedule and format for both the self-guided and clinician-guided intervention groups over the duration of study participation.

Format of data collection	In person	Remote					
	Before the intervention	During the intervention			After the intervention		
	Week 0	Week 2	Week 4^a^	Week 8	Week 12	Week 26	Week 52
Randomization	✓						
Tendon Health Domains (Performance-based)	✓		✓	✓			✓
Tendon Health Domains (Survey-based)	✓	✓	✓	✓	✓	✓	✓
Ultrasound imaging	✓						
Clinical variables	✓		✓	✓	✓	✓	✓

a Week 4 indicates primary end point.

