### Primary Outcomes

The primary outcomes of this study are movement pain and disability (Table 3). Movement pain will be measured using the NRS. Assessing the participant’s worst pain during single-limb heel raises allows for comparison of outcomes with previous clinical trials for AT [26,28-30]. Disability will be measured using the VISA-A, which assesses disability specific to AT and allows comparison to other studies, as this is the most commonly used self-reported outcome for AT [31-34].

**Table 3. T3:** Measures and psychometric properties used in the PACE (progressive Achilles loading via clinician e-support) study^a^.

Health domain	Measure	Psychometric properties
Pain	Pain with movement during single-limb heel raises [26,28-30] and hops^b^^,^^c^ Pain at rest^c^	MID^d^ 1.1 (95% CI 0.9-1.6) [35] on a 0‐10 NRS^e^ MID for PACE1.7 [36] on a 0‐10 NRS
Disability	VISA-A^b^^,^^f^^,^^g^ [37,38] Tendinopathy severity assessment^c^ [39]	MID 8.2 (SD 16.3) [40] Cronbach *α*=0.808 Reliability: ICC^h^ 0.930 (95% CI 0.881-0.959) Standard error of measurement=6.54 units [41]
Physical function and capacity	PROMIS^f^^,^^i^ physical function CAT^j^ [42] Maximum number of single-limb heel raises^c^ [43] Heel raise work^c^	Internal consistency: person reliability=0.96 Item reliability=0.99 [44] Test-retest reliability: ICC 0.83 (95% CI 0.63-0.92) [45] Interrater reliability: ICC 0.99 (95% CI 0.88-0.99) Criterion validity: ICC 0.97 [46]
Psychosocial factors	Tampa Scale of Kinesiophobia (17-item)^f^ PROMIS Self-Efficacy CAT^f^ [42] Optimal Screening for Prediction of Referral and Outcome-Yellow Flag tool (17-item)^f^ PROMIS Sleep Disturbance CAT^f^ [47]	Cronbach *α*=0.70‐0.83 Test-retest reliability: *r*=0.64‐0.80 Concurrent validity: *r*=0.33‐0.59 [48] Concurrent validity with legacy measures: *r*=0.59‐0.76 [49] Test-retest reliability: ICC 0.88; *P*<.001 [50] Internal consistency, marginal reliabilities=0.92 Test-retest reliability, *r*=0.80 [47]
Patient rating of condition	Patient Acceptable State^f^ [51] Patient Global Rating of Change^f^ [52]	Concurrent validity [53] PROMIS Pain Interference <56.0 (AUC^k^ 0.940) PROMIS Pain Intensity <48.4 (AUC 0.936) PROMIS Physical Function >44.7 (AUC 0.883) Test-retest reliability: ICC 0.90 Face validity: Pearson *r*=0.72‐0.90

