Participation in life activities	PROMIS Ability to Participate in Social Activities CAT^f^ [54] PROMIS Pain Interference CAT^f^ [44]	Reliability >0.90 Sufficient unidimensionality root mean square error approximation=0.108 Cronbach *α*=0.96 [55] Concurrent validity with brief pain inventory: *r*=0.76 (95% CI 0.64-0.85); *P*<.01
Quality of life	World Health Quality of Life–2^f^ [56] (subset of the first 2 items on the WHOQOL-BREF^l^)	Cronbach *α*=0.51-0.82 for entire WHOQOL-BREF

a Primary outcomes are movement pain as measured with the NRS and disability measured with the VISA-A.

b Primary outcome.

c Tendon health domain (performance-based measure).

d MCID: minimal important difference.

e NRS: numeric rating scale.

f Tendon health domain (survey-based measure).

g VISA-A: Victorian Institute of Sport Assessment–Achilles.

h ICC: intraclass correlation coefficient.

i PROMIS: patient-reported outcome measure information system.

j CAT: computer adaptive test.

k AUC: area under the curve.

l WHOQOL-BREF: World Health Organization Quality of Life–Brief.

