### Data Analysis

Baseline characteristics will be presented as counts and percentages for categorical measures. Continuous measures will be reported as means and SDs or medians and IQRs, as appropriate. Summary statistics by group will be provided for the primary and secondary outcomes and will be compared using 2-sample *t* tests, Wilcoxon rank-sum tests, or Fisher exact tests, as appropriate. Our intention-to-treat analysis will use linear mixed-effects models to assess the noninferiority of the single-visit intervention compared to the multivisit intervention, adjusting for baseline values of the primary outcomes. Additional intention-to-treat analyses will include any covariates that differed between groups at baseline. Primary outcomes will be the 4-week changes in measures of pain and function, and models will account for site using a random effect. Point estimates, CIs, and *P* values will be obtained for between-group differences in 4-week mean change compared to the margin of noninferiority. Significance for testing pain and function will be assessed at an *α* level of .025. We plan to report all data disaggregated by sex, AT type, and AT duration.

Secondary analyses will use linear mixed-effects models to examine predictors of improvement in pain and disability separately at 4 weeks. The same analysis will be performed at 12, 26, and 52 weeks as secondary end points. Outcomes will be the changes measured at each follow-up time point, and the models will be controlled for the corresponding baseline values. Model selection will be conducted to identify the optimal predictor set for each change outcome over time. The pool of candidate predictors includes baseline demographic and ultrasound imaging variables, as well as immediate improvement (within 2 weeks) of pain-related psychological factors, knowledge on self-management, pain, and disability. Models for all additional predictor combinations up to order 3 will be fit, and the Akaike information criterion will be calculated to compare model fits with the same outcome. Point estimates, CIs, and *P* values will be reported for predictors in models selected by the Akaike information criterion for each outcome. Significance for model predictors will be assessed at an *α* level of .05. Categorization of continuous variables using clinically meaningful cut points, such as obesity categories for the continuous BMI variable, will also be explored.

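### Movement pain is not scheduled at weeks 2, 12 or 26, but the prognostic aim uses pain change at exactly those weeks

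*Protocol article*

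**What the plan says.** The second aim is prognostic. In the Introduction, the hypothesis is that "individuals with greater immediate (within 2 weeks) improvements in self-efficacy, pain, and disability" will benefit most from rehabilitation. Data Analysis carries this forward: the candidate predictors include "immediate improvement (within 2 weeks) of pain-related psychological factors, knowledge on self-management, pain, and disability". The outcomes modelled are change in pain and change in disability, separately, at 4 weeks, and then: "The same analysis will be performed at 12, 26, and 52 weeks as secondary end points".

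Primary Outcomes defines the pain measure as an NRS score taken during a physical task: "Assessing the participant’s worst pain during single-limb heel raises allows for comparison of outcomes with previous clinical trials for AT". In Table 3, movement pain (heel raises and hops) and pain at rest both carry footnote c, "Tendon health domain (performance-based measure").

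Outcome Measures sets the schedule: "Participants will complete 3 survey-only evaluation sessions at 2, 12, and 26 weeks". Weeks 4, 8 and 52 are video sessions, and "The video evaluation sessions will be used to capture pain with tendon-loading activities (heel raises and hops) in real time".

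**The concern.** The weeks at which the analysis needs pain and the weeks at which pain is scheduled do not match. Early change in pain is one of three predictors named in the hypothesis, and it requires a week 2 score that the schedule does not provide. The repeated pain models need week 12 and week 26 scores that the schedule also lacks.

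If this stands, the analysts must either drop part of the second aim or choose a substitute measure later. A late substitution would be especially awkward here, because predictors are chosen by an Akaike information criterion search over combinations, and swapping in another pain variable adds an unplanned choice to that search. Unlike most analysis details, uncollected data cannot be put right before database lock.

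**Working it through.** The article states no figure to reproduce, so the check compares schedule with requirement.

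**Inputs**

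- Class of the measure: movement pain and pain at rest are performance-based (Table 3, footnote c). VISA-A is survey-based (footnote f).
- Table 2, row "Tendon Health Domains (Performance-based"): ticked at weeks 0, 4, 8 and 52; blank at weeks 2, 12 and 26.
- Table 2, survey-based row: ticked at every visit.
- Session text in Outcome Measures: it puts heel-raise and hop pain in the video sessions (weeks 4, 8 and 52) and makes weeks 2, 12 and 26 survey-only. This agrees with Table 2 and does not depend on the Table 3 footnotes.
- Required weeks: 0 and 2 for the early predictor; 0 plus each of 4, 12, 26 and 52 for the change outcomes (Introduction and Data Analysis).

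**Cross-check**

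| Quantity needed | Weeks needed | Movement pain scheduled? | VISA-A scheduled? |
|---|---|---|---|
| Early improvement (predictor) | 0, 2 | No | Yes |
| Change at week 4 | 0, 4 | Yes | Yes |
| Change at week 12 | 0, 12 | No | Yes |
| Change at week 26 | 0, 26 | No | Yes |
| Change at week 52 | 0, 52 | Yes | Yes |

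**Counts**

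- Hypothesised early predictors (self-efficacy, pain, disability) without NRS data: 1 of 3.
- Pain-outcome models without an outcome: weeks 12 and 26, so 2 of the 4 time points, or 2 of the 3 after week 4.
- Models that cannot include the early movement-pain predictor: 2 outcomes × 4 time points = 8 of 8.
- Participants not yet enrolled at the January 2026 count: 160 − 15 = 145, and 145/160 = 90.6%, about 91%.

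Incidentally, movement pain is collected at week 8, which is not among the analysis time points. That is not an error in itself, but it shows that the two lists of weeks were not aligned.

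**The case against.** The strongest reply is that the article never says outright that the surveys hold no pain rating. The Methods overview names the two primary outcomes and then lists assessments at 2, 4, 8, 12, 26 and 52 weeks without excepting pain. A rating of pain at rest needs no performance, so its footnote could be a labelling slip. The hypothesis and predictor list say pain, not movement pain, and PROMIS Pain Interference is survey-based and collected at every visit. On this view, the early predictor is merely unnamed, which an analysis plan could settle.

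Part of this stands. For the predictor, another pain variable could have been intended, and the survey forms are not shown. But the conflict remains:

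- The general list of weeks in the overview conflicts with the specific schedule; it does not resolve it.
- A corrected label for pain at rest would not supply movement pain, which is the defined outcome.
- Table 3 files PROMIS Pain Interference under participation in life activities, and nothing names it as the pain outcome or predictor.
- For weeks 12 and 26, repeating the same analysis implies the same outcome, so a different measure is not a natural reading.
- The multiple imputation in the Missing Data section addresses values that were scheduled and lost. It has no observed week 2, 12 or 26 scores to learn from.

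It is also fair to say that the damage is confined to the prognostic aim, and that the omission of week 8 is a matter of preference.

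**Conclusion.** The concern holds. On the article's own schedule, the 2-week movement-pain predictor and the week 12 and week 26 movement-pain outcomes do not exist for any of the 160 planned participants. Those parts of the second aim cannot be run as written.

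The scope is limited. The week 4 noninferiority analysis, the VISA-A outcome data at every time point, and the pain outcomes at weeks 4 and 52 are all available. The conclusion assumes that Table 2 and the session text describe what is actually collected, and that pain in the secondary analyses means the co-primary movement-pain score. If the survey forms already contain an NRS pain item, the fault lies in the schedule text, which must then be corrected and the item named.

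This should be fixed now. It concerns one of the trial's two stated aims, and each missed visit is an irrecoverable loss.

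**What to change.** Preferred: add one NRS item to the week 2, 12 and 26 surveys, asking for worst pain during self-performed single-limb heel raises and worded as in the video session. Update Tables 2 and 3 to show it.

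Alternative, if no item is to be added: restrict the movement-pain models to weeks 4, 8 and 52, and replace early change in pain, in both the hypothesis and the predictor list, by a named survey measure already collected at week 2.

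The first option costs one REDCap item and a minor amendment. Self-performed ratings are less standardised than those taken in a video session, and change scores would mix an in-person baseline with unobserved follow-up; the report should say so. Participants already past week 2 will lack the early item. Because enrolment began in August 2025, week 26 still lay ahead for nearly all of the first 15 at the January 2026 count. The 91% is therefore the share that could provide all three time points, and it falls as enrolment continues without the change.

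The second option needs only a text change and avoids mixing modes, but it gives up the week 12 and 26 pain models and tests a different early predictor.

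### Aim 2 reports CIs and P values at .05 from the AIC-selected model with no allowance for the search, and the hypothesised 2-week predictors get no pre-specified test

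*Protocol article*

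**What the plan says.** The Introduction of the Protocol article states a directional hypothesis for Aim 2: the greatest benefit will go to "individuals with greater immediate (within 2 weeks) improvements in self-efficacy, pain, and disability".

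The Data Analysis section sets out how Aim 2 is analysed:

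- Linear mixed-effects models will "examine predictors of improvement in pain and disability separately at 4 weeks", and the analysis is repeated at 12, 26 and 52 weeks. The response is change from baseline, with the baseline value of the outcome in the model.
- "The pool of candidate predictors includes baseline demographic and ultrasound imaging variables, as well as immediate improvement (within 2 weeks) of pain-related psychological factors", together with 2-week improvement in self-management knowledge, pain and disability. The number of candidates is not given.
- "Models for all additional predictor combinations up to order 3 will be fit, and the Akaike information criterion will be calculated to compare model fits".
- "Point estimates, CIs, and *P* values will be reported for predictors in models selected by the Akaike information criterion for each outcome".
- The threshold for each of these tests is .05.
- Cut points for continuous predictors will be explored as well.

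The section names no sample split, bootstrap of the selection, shrinkage or multiplicity control for this step. It does not call these P values descriptive or exploratory.

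**The concern.** A P value or interval from a model has its nominal meaning when the model was fixed before the data were seen. Here the same data first pick the winner from a large set of models and then supply its tests. The predictors that reach the table are there because they looked strong in this sample, so their P values are too small and their intervals sit too far from zero.

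The hypothesised predictors are exposed to the same process. If AIC drops the 2-week change in self-efficacy, the plan reports no estimate for it. If AIC keeps it, its P value is a post-selection one. Either way, the stated hypothesis is not tested as stated.

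What is at stake is Aim 2. The Introduction wants prognostic factors to help separate likely responders from patients who may move on to invasive treatment. False factors would mislead that use.

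**Working it through.** **The plan's own figures.** The Power Calculation section gives 64 evaluable participants per group and 20% dropout: 64 / (1 − 0.20) = 80 per group, 160 in total. This reproduces. Evaluable n = 2 × 64 = 128. For Aim 2 the only error-rate figure is the nominal .05, so that is the figure to check.

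**Size of one search.** Reading order 3 as at most three predictors, the number of models for p candidates is 1 + p + C(p,2) + C(p,3):

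- p = 6: 1 + 6 + 15 + 20 = 42
- p = 10: 1 + 10 + 45 + 120 = 176
- p = 15: 1 + 15 + 105 + 455 = 576
- p = 20: 1 + 20 + 190 + 1140 = 1351

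The range of 6 to 20 is my assumption, because the pool size is not stated.

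**Approximation by hand.** AIC keeps an extra predictor when its likelihood-ratio statistic exceeds 2, and P(χ² on 1 df > 2) = .157. A noise predictor in the winning model has therefore already passed a screen at about P<.157. Given that, the chance that its nominal 95% CI covers zero is about 1 − .05/.157 = 68%. The chance that at least one of p independent noise candidates has P<.05 is about 1 − 0.95^p: 26%, 40%, 54% and 64% for p = 6, 10, 15 and 20.

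**Simulation of the described procedure.** The baseline value is forced in, all subsets of 0 to 3 candidates are fitted, the lowest AIC is kept, and ordinary t-based P values and 95% CIs are taken from the winner. Predictors are normal, none has a true effect, and the site random effect is omitted.

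| Candidates | At least one P<.05, n=128 | At least one P<.05, n=160 | CI coverage of selected predictors, n=128 |
|---|---|---|---|
| 6 | 28.7% | 28.2% | 67.1% |
| 10 | 43.6% | 42.0% | 64.9% |
| 15 | 57.5% | 57.7% | 61.1% |
| 20 | 70.9% | 69.9% | 54.1% |

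Separate runs of the same check reach 75% for 20 candidates, with coverage between about 53% and 69%. If candidates correlate 0.3 (n=128), the chance of a false predictor is 50% for p = 10 and 69% for p = 15.

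**With one real predictor.** Take a standardized effect of 0.2 and n=128. For p = 10 and 15, a false predictor is still declared in 40% and 58% of trials. CIs over all selected predictors cover 75% and 67%. The real predictor's own CI covers 97% and 95% when it is selected, but its estimate is about 18% too large.

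**What a .05 error rate would need.** To hold the chance of any false predictor in one null search at 5%, the nominal cut-off would have to be about .0074, .0041, .0024 or .0019 for p = 6, 10, 15 or 20.

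**Number of searches.** Two outcomes at four time points would be 2 × 4 = 8. However, Table 3 marks movement pain as performance-based, and Table 2 schedules performance-based measures only at weeks 0, 4, 8 and 52. As scheduled, movement pain can be analysed at 4 and 52 weeks and disability at 4, 12, 26 and 52 weeks, which gives 2 + 4 = 6 searches.

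**The case against.** The strongest defence is that this is a secondary analysis, that AIC is a legitimate exploratory tool, and that bootstrap validation or hypothesis-specific models may sit in an analysis plan not shown. AIC selection is indeed no error in itself. But the article does more than leave a gap: it states that CIs and P values come from the selected model and fixes .05 as their threshold. An analysis plan would have to change that text.

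It is also fair that the figures rest on an assumed pool size and, in the table, on no true predictor. With a real predictor present its own interval covers about nominally, so it would be wrong to say that all intervals fail. The damage sits mainly with noise variables that were selected.

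A reader might go further and infer that 2-week VISA-A change is bound to be significant because it is part of the 4-week change. The documents do not support that. The models control for baseline, and regressing Y4 − Y0 on (Y2 − Y0, Y0) gives the same slope and test for the week-2 term as regressing Y4 on (Y2, Y0). When week 2 adds nothing given baseline, the plan's test rejects in about 4.6% of runs. Rejection in 100% of runs appears only under added assumptions: early gains that persist fully, or a stable trait with measurement error (assumed reliability 0.8). Such a result would show that the week-2 score carries information beyond baseline, and no more than that.

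Switching the response to change from week 2 onward would make matters worse, because Y2 then enters both sides with opposite signs and the slope falls by 1. In the case just described it is spuriously significant in 100% of runs. With independent true changes of assumed SD 10 and the standard error of measurement of 6.54 from Table 3, it is spuriously significant in about 76%. It also departs from the stated target of improvement by 4 weeks.

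**Conclusion.** The point holds for Aim 2. As written, the .05 threshold and the 95% intervals do not have their stated properties. With no true predictor, n=128 and 6 to 20 candidates, a single search gives at least one false significant predictor in roughly 28% to 75% of trials, and intervals of selected predictors cover about 53% to 69%. One modest real effect leaves the false-predictor rate at 40% to 58% for 10 to 15 candidates. Exploring cut points adds further selection that these figures leave out.

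The size depends on the assumed candidate count and on reading order 3 as up to three predictors; if it means interactions, the search is larger. The Introduction's hypothesis about 2-week improvements has no test of its own. Aim 1 does not use this selection and is not affected. The change should be made, and it is not urgent: 15 participants were enrolled by January 2026 and enrolment runs to 2028.

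**What to change.** - For each outcome, test the hypothesised 2-week changes in one pre-specified model that includes the baseline value, arm, site and the stratification factors. Keep change from baseline as the response.
- Name the week-2 pain measure. Movement pain is not scheduled at week 2, so the pain predictor has to be one that is actually collected then, or the schedule and the hypothesis have to be reconciled.
- Label the AIC search exploratory. List the candidates, say what order 3 means, bootstrap the whole selection, and report selection frequencies and optimism-corrected performance.
- Make no P<.05 claims from the selected model, and state which outcomes are searched at which time points in line with Table 2.

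The cost is revised wording and some bootstrap programming, with no new participants. Fewer predictors can be called significant.

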Recent evidence has shown that overtreatment of musculoskeletal disorders does not lead to improved outcomes. Hopewell et al [17] found that a single session of education and self-management advice with a PT was noninferior to 6 sessions of in-person progressive exercise in improving pain and function among individuals with subacromial shoulder pain. Similarly, Katz et al [18] found that a self-directed home exercise plan alone was noninferior to 14 sessions of PT-guided exercise and manual therapy for pain reduction in individuals with meniscal tear–related knee pain. AT is lacking in trials to gauge the minimal effective dosage of exercise interventions. Pivoting to expand access through novel care delivery pathways is now more feasible, given the evidence that pain and function can improve with focused minimal care [19].

Clinicians currently lack evidence-based prognostic factors to differentiate patients who will benefit from rehabilitation from those who are less likely to respond [20,21]. Given that 26% to 47% of individuals with AT proceed to injections or surgery [22-24], the identification of prognostic factors could inform more efficient and personalized care. For nonresponders to rehabilitation, delays in progressing to invasive treatments prolong Achilles tendon pain, waste patient time and health care resources, and increase the total number of limited duty days as multiple treatments are tried. There is a critical need for a large, prospective study to identify factors that predict which patients with AT are most likely to respond to rehabilitation.

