## Discussion

Exercise and education have been shown to be effective for the management of AT [4,23,24,26,28,60,61], but to date, no studies have been conducted to gauge the minimal effective dosage of exercise and education interventions or to identify prognostic factors for success with noninvasive treatments in patients with AT. This randomized controlled trial will identify a rehabilitation program focused on education and exercise for AT that expands access to care and will identify factors that predict responses to rehabilitation. This will be accomplished by determining the efficacy of a single-visit, PT-initiated rehabilitation program compared to a multivisit, PT-guided rehabilitation program for AT and by identifying early prognostic factors for individuals who experience the greatest improvement in pain and disability by 4 weeks. 

This trial comprises a robust sample of both midportion and insertional AT. A large heterogeneous sample (N=160) will provide adequate power to detect multiple factors that most strongly predict the success of rehabilitation for AT. Including both subtypes of AT and a range of symptom duration (acute vs chronic) will better represent the natural heterogeneity of the population with AT presenting for care and facilitate the ability to detect potential predictors. Maximizing patient heterogeneity in prognostic studies allows models to account for a wider range of characteristics and factors that may influence outcome prediction, enhancing generalizability to diverse real-world populations and clinical settings [62].

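### Aim 2 accepts prognostic factors on significance after AIC selection, with no absolute or optimism-corrected measure of prediction, so factors that barely predict outcome can be reported as predicting response

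*Protocol article*

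**What the plan says.** The Introduction sets the second aim as "to identify early prognostic factors for individuals who experience the greatest improvement in pain and disability by 4 weeks". The need it cites is that clinicians lack "prognostic factors to differentiate patients who will benefit from rehabilitation from those who are less likely to respond". The Discussion says that N=160 gives adequate power to "detect multiple factors that most strongly predict the success of rehabilitation for AT".

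The Data Analysis section fixes how this is done:

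- Outcome: "Outcomes will be the changes measured at each follow-up time point, and the models will be controlled for the corresponding baseline values". This is a continuous change score, and no responder is defined.
- Selection: "Models for all additional predictor combinations up to order 3 will be fit, and the Akaike information criterion will be calculated to compare model fits" for the same outcome.
- Output: point estimates, CIs and P "values will be reported for predictors in models selected by the Akaike information criterion for each outcome".
- Criterion: "Significance for model predictors will be assessed at an" α level of .05.

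For Aim 2 the article names no R², prediction error, discrimination, calibration, cross-validation or optimism correction. The AUC values in Table 3 are psychometric properties of instruments, not planned analyses.

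**The concern.** The aim is about telling patients apart. The planned output is about association in the data used to choose the model. A coefficient with P<.05 does not show whether knowing the factor improves on the baseline score when predicting a patient's change. AIC does penalise complexity, but it gives only a relative ranking, and its penalty counts the terms in each model, not the number of models searched. The CIs and P values are then computed as if the chosen model had been fixed in advance, so they are too optimistic.

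At stake is the Aim 2 conclusion. Followed as written, the rule can present a factor set as predicting response when it would not help to sort new patients, and the planned output would not reveal this.

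**Working it through.** **Sample size.** The Power Calculation section gives 64 per group and 20% dropout: 64 / (1 − 0.20) = 80 per group, 160 in total. This reproduces the plan's figure and leaves 2 × 64 = 128 completers.

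**Weakest factor that reaches P<.05.** For a factor fixed in advance, r² = t² / (t² + df), taking df = n − 4. With n=128, df=124 and t=1.979, r² = 3.917 / 127.917 = 0.0306, so r = 0.175. Under bivariate normality, with a good outcome defined as above-median change:

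- AUC is 0.58, where 0.50 is no separation.
- A median split places 0.5 + arcsin(0.175)/π = 0.556 correctly, so about 56% do well in the better half and 44% in the worse half.
- Residual SD falls by 1 − √(1 − 0.0306) = 1.5%.

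With all 160 analysed, the threshold is r = 0.156 (2.4% of variance, AUC 0.57).

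**Weakest factor that AIC keeps.** Adding one term lowers AIC when partial R² exceeds 1 − exp(−2/n). At n=128 this is 1.55%, or AUC 0.56. AIC is therefore the looser of the two screens.

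**Effect of the search.** The article gives no candidate count, so 8 to 20 is assumed, and order 3 is read as up to three added predictors. For 12 candidates the number of models is 1 + 12 + 66 + 220 = 299. Simulated trials used n=128, independent candidates, a baseline-adjusted linear model without the site effect, and the lowest-AIC model.

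With pure noise, the chosen model kept at least one predictor in 78%, 88% and 97% of trials for 8, 12 and 20 candidates. At least one predictor had P<.05 in 36%, 50% and 72%.

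With 12 candidates and at most one true factor, the gain in R² over the baseline-only model was as follows (ranges are across repeated runs):

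| True partial r | Apparent gain | Gain in new patients | Worse than baseline alone |
|---|---|---|---|
| 0 | 5.4% | −5.6% | – |
| 0.2 | 8.5% to 9.4% | −1.6% to −2.4% | 62% to 68% of trials |
| 0.3 | 13.2% | about +4% | 9% to 13% |
| 0.4 | – | +11.7% | 0% |

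At r=0.2, 79% of trials had at least one selected predictor with P<.05, and 69% of those still predicted worse than baseline alone. The significance criterion did not screen out non-predictive models.

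**Sensitivity.** At r=0.2 the share worse than baseline is 43% to 52% with 8 candidates and 82% to 88% with 20. With 12 candidates and n=160 it is 48%. At r=0.3 it is 4% with 8 candidates and up to 30% with 20. With 12 candidates and two true factors at 0.3, it is 0% and the gain in new patients is +14.0%.

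**The case against.** The strongest reply is that this is a condensed article and that performance measures for a secondary analysis usually belong in a SAP, which is not shown. That would answer a complaint about missing detail only. Here the article itself states the selection rule, the output and the .05 criterion, and the point rests on what those produce.

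Second, a reader might infer that predictors are judged by P values alone and never by anything related to prediction. The article does not support that. AIC is related to expected prediction error, and CIs are reported. What stands is that AIC is relative and takes no account of the search, and that the CIs ignore the selection.

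Third, a reader might infer that weak factors will be reported, or that the chosen model will usually fail. The article does not support that either. A weak factor must first be selected and significant, and its CI may show that the effect is small. The leading candidates include 2-week improvements in the outcome scores themselves, so stronger effects are plausible, and at r=0.3 or above the chosen model usually helps. The Missing Data section also plans multiple imputation, so 128 complete cases is an approximation to the analysis set.

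Fourth, no triage rule or risk score is planned, and adjusted associations are a legitimate result for prognostic-factor work. That is fair. However, the Introduction and Discussion claim more than association, and the planned output cannot support that extra claim.

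**Conclusion.** The point holds as a statement of what can happen. Under the stated rule, a factor explaining about 3% of variance (AUC about 0.58 at n=128) qualifies as a predictor. So does a chosen model that does no better in new patients than the baseline score. The 3% threshold follows from the sample size alone; the AUC also assumes normality and a median split. The frequency of failure does not follow from the article. It rests on an assumed candidate count, independent candidates and the true effect sizes: with 12 candidates, about 62% of trials at r=0.2 and about 9% at r=0.3. The planned output cannot reliably distinguish these situations, and that is the defect. It affects one of the trial's two aims and leaves the noninferiority comparison untouched.

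**What to change.** For each outcome, with 4 weeks as the main time point, report the gain in R² and in prediction error of the selected model over a model with the baseline score only. Correct both for optimism by bootstrapping the full selection procedure, including the all-subsets search and any exploration of cut points, and give the corrected gain with its uncertainty. Call a factor set predictive only where that corrected gain supports it; a point estimate just above zero is not enough. Otherwise, describe the results as associations.

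AUC for reaching 1.1 NRS points or 8.2 VISA-A points is an optional supplement. It dichotomises a continuous outcome and needs a responder definition that the Data Analysis section does not give.

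The cost is analysis code and one table, with no new data. The Aim 2 headline may become less favourable. Enrollment is expected to run until 2028, so this can still be prespecified.
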